## Abstract

**Background:** Schizophrenic psychoses are severe mental disorders. Despite advances in treatment, outcomes are still unsatisfactory. Pharmacological treatments are still limited, in particular regarding improvements in psychosocial functioning and neuro-cognitive impairment. In recent years new psychological therapies have been developed, demonstrating promising results. However, most of these interventions have been designed for and studied in outpatients; their efficacy and feasibility for patients requiring hospitalization is still unknown. Therefore, we have designed a clinical trial to compare a neuro-cognitive (Integrated Neuro-cognitive Treatment INT); a cognitive-behavioral (Integrated Psychological Therapy IPT); and a control (Cogpack CGP) intervention for patients with a schizophrenic psychosis hospitalized for treatment.

**Methods:** In a three-parallel-arm, single-blind, randomized, controlled study, we compare INT, IPT, and CGP. Participants will take part in two weekly sessions of one intervention for at least 16 sessions. If due to randomization, participants are allocated to a treatment arm not suitable for them, they are allowed to switch intervention after four sessions. Based on a sample size calculation, recruitment will continue until 30 participants have completed the intervention for each treatment arm.

**Outcome Measurement:** Primary outcomes are: change in symptom as measured by the Positive and Negative Syndrome Scale (PANSS), change in psychosocial functioning as assessed by the mini ICF-APP and neuro-cognitive performance, assessed by the Matrics Cognitive Consensus Battery (MCCB). Other outcomes of interest are the Brief Symptom Inventory (BSI) and the Health of the Nation Outcome Scales (HoNOS); together with prescribed medication, treatment retention and completion rates. Outcomes will be measured at baseline, 2 weeks into treatment (prior to a potential switch of intervention arm), post-treatment and at 6 and 12-month post-treatment follow-ups.

**Expected Outcomes:** We expect an overall improvement; however, with differences in specific domains for each treatment arm, with those completing INT showing better outcomes than IPT and CGP, respectively. We anticipate that lower functioning participants will drift to CGP and higher functioning participants to INT.

**Conclusion:** Due to the complexity of treatment for patients with a schizophrenic psychosis, we consider it crucial to compare different treatment options for those more severely affected, therefore, requiring inpatient treatment.

**Trial registration:**
www.clinicaltrials.gov (ID: NCT03316664; 17.10.2017).

## Background

Schizophrenic psychoses are severe mental disorders, with a heterogeneous combination of symptoms and a lifetime prevalence of around one per cent (1, 2). Characteristic symptoms, albeit not exclusive, are hallucinations, delusions, apathy, blunting of affect, disorganized speech and thinking, together with cognitive impairment (3). Those affected are struck in the prime of life and are frequently unable to cope with the challenges of everyday life; experiencing impairment and disability in multiple domains, including the ability to maintain social relationships, sustain employment, and live independently (1, 2).

The treatment of schizophrenic psychoses remains a challenge; only around half of the patients show substantial clinical improvement (4). Treatment of Schizophrenia still relies predominantly on antipsychotic agents (5). Since their clinical introduction over 60 years ago, the Dopamine D2 receptor antagonism remains the pivotal mechanism of action. Newly developed antipsychotics follow the strategy of maintaining this effect, while attempting to improve tolerability (5). The pharmacological treatment of schizophrenia is often limited due to side-effects (6–8). Overall, antipsychotic agents are most effective in reducing positive symptoms, in comparison other symptom domains, such as psychosocial functioning, negative symptoms, and cognition show minimal improvement (5, 9).

In the past few decades, psychological interventions have been shown to be effective when used in conjunction with pharmacological treatment (10, 11). Psychoeducation, assertiveness training, family therapy, cognitive behavioral therapy, and cognitive remediation treatment programs have been developed and systematically studied and further improved (10–15). Current guidelines recognize their importance for treatment and outcome, correspondingly implementation early on in treatment is recommended, even in hospitalized patients (16–19). However, current evidence regarding the effectiveness of psychotherapeutic interventions has been obtained primarily in studies of outpatient populations; studies in chronic and low functioning patients hospitalized for treatment are sparse (20, 21), with patient recruitment a major challenge (22).

The Integrated Psychological Therapy (IPT) for patients with schizophrenia is one of the first manualized integrated cognitive remediation therapy programs for groups, combining social skills, neuro- and social cognition in a single therapy (23, 24). Since the first trial in 1980, IPT has been extensively studied, with empirical evidence consistently demonstrating its efficacy; consequently, it is currently implemented in clinical practice (25). The further development of IPT has led to Integrated Neurocognitive Therapy (INT) for Schizophrenia, a manualized cognitive remediation therapy, which includes a computerized neurocognitive training component (Cogpack CGP) (26, 27). In clinical trials INT has been shown to not only improve neuro- social-cognitive performance but also to have the potential to improve functional outcome and to reduce negative symptoms (24, 27–29).

Although both INT and IPT seem to be effective treatments for patients with schizophrenia; the therapeutic approaches differ in terms of the symptoms they address, together with how the intervention is delivered (29, 30). Through its plain and straightforward design, IPT is suitable for chronic and hospitalized patients (31). However, IPT does not target all the cognitive domains impacted in schizophrenia (32). In contrast, INT not only integrates these cognitive domains in its therapeutic approach, it also includes elements designed to improve self-awareness and perception of the environment. Furthermore, it includes a computer-based cognitive training, with effects of its own. Consequently, INT is a more complex and challenging intervention than IPT for both therapists and participants (29). Primarily for this reason, INT trials to date have been conducted almost exclusively in outpatient settings (29, 30).

Generally, outpatients are less severely ill (33), which may have implications regarding the implementation of INT for patients requiring hospitalization for treatment. To the best of our knowledge, there have been no trials directly comparing IPT to INT; it is therefore not known if both therapy approaches are equally effective or if one program works better for certain patients or is indeed detrimental for others. Important factors which need to be taken into account are the symptom load and severity in patients requiring hospitalization for treatment, the conditions of the treatment unit, in particular fluctuation in the patient population, together with the presence of patients with disturbing behavior (21).

Therefore, we plan to conduct a single-blind, randomized, controlled trial comparing INT, IPT, and CGP in patients with schizophrenia requiring hospitalization for treatment; to assess the efficacy and feasibility of INT as a treatment programme for such patients. The main outcomes for the assessment of efficacy are changes in symptom load and functionality, together with cognitive performance. Outcomes for feasibility are retention, switch rates, and overall therapy attendance.

## Methods

### Design

We have designed an 8-week, randomized, controlled, assessor-blind, three-parallel-arm trial for patients diagnosed with a schizophrenic psychosis. All patients with the diagnosis of a schizophrenic psychosis (according to the DSM 5 Diagnostic criteria) are eligible to participate. In order to allow the participation of chronic and low-functioning patients, the inclusion criteria were deliberately broad (see Table 1).

**Table 1 T1:** Inclusion and Exclusion criteria.

**Inclusion criteria**
Participants are competent to give informed consent, as determined by the referring physician or psychiatrist.
Diagnosis of Schizophrenia or Schizoaffective Disorder according to DSM-5 (34)
Participants are between 18 and 65 years of age.
Completion of regular compulsory education.
German language proficiency as a native speaker or level B1 Common European Framework of Reference for Languages (CEFRL) (35)
**Exclusion criteria**
Unwilling or unable to comply with study instructions.
Low Intelligence as confirmed by failure to complete regular compulsory education.
Currently in another psychotherapeutic treatment, either in individual or group sessions.
Current consumption of alcohol or illicit drugs.

### Recruitment

The Center for Integrative Psychiatry [ZIP: (German) Zentrum für Integrative Psychiatrie], is part of the Psychiatric University Hospital of Zurich specializes in treating “heavy-users,” i.e., those patients with frequent or long-term hospitalizations for whom outpatient treatment is often insufficient. Participants will be recruited among the patients hospitalized for treatment in the Unit for Psychotic Disorders of the ZIP.

### Interventions and Therapists

Cogpack is a computer-based neuropsychological cognitive training program, covering seven domains: visual-motor skills; processing speed; vigilance; executive functions; memory; verbal comprehension and problem- solving (26, 36). Tasks employed will be identical to those used in the INT sessions. The difficulty level of each task is adapted automatically by the program. At the end of each task, the computer program generates a feedback-report for every user on their performance including “percentage correct” and “completion speed.” Cogpack will be delivered by a psychiatric medical resident, with cognitive behavioral training and a 2-h introduction to the computer program followed by practical training.

Integrated Psychological Therapy (IPT) is a manualized psychological intervention consisting of five modules (37). The five modules are hierarchically arranged and deal with cognitive deficits, perceptual deficits, verbal communication, social skills, and problem-solving, with successively increasing complexity in each module. The procedure and contents for each module are broadly predefined and can be adapted to each group's specific needs. Therapists delivering IPT are nurses (as IPT has been traditionally delivered) with basic training in cognitive behavioral methods and a 3-day seminar on IPT followed by practical training and regular supervision.

Integrated Neurocognitive Therapy (INT) is a manualized psychological intervention consisting of four modules. Each module consists of neuro- and social-cognitive elements, together with stress and emotional regulation domains. The complexity of the modules increases successively as do the emotional demands. INT has a strategy-based-learning and a drill-and-practice approach, where the same didactic structure is applied to each domain (27, 38). One peculiarity feature of INT is the integration of cognitive domains, together with self-awareness/perception; and computer exercises (CGP) (26). Therapists delivering INT have a psychology and psychotherapy degree and have attended a 3-day seminar on INT, followed by practical training and receive regular supervision.

Taking into account the usual length of stay in our unit, together with current recommendations, we have adapted both IPT and INT to 20 session programmes comprising the contents of all modules, whilst respecting the specifications and recommendations of the manuals. Cogpack modules are analogous to those of INT. For an overview of the parallel interventions according to TIDieR (see Table 2).

**Table 2 T2:** Content and chedule of Interventions (ToM: Theory of Mind).

	**IPT**	**INT**	**CGP**
**First Block**	**Module 1**	**Module A**	**Module A**
Sesion 1	Card sorting	Information processing	Information processing
Sesion 2	Verbal concept	Attention/vigilance	Attention
Sesion 3	Verbal concept	Perception of emotions	Attention
Sesion 4	Search strategies	Perception of emotions	Vigilance
**Second Block**	**Module 2**	**Module B**	**Module**
Sesion 1	Information collection	Verbal and visual learning	Verbal and visual learning
Sesion 2	Interpretation and discussion	Memory	Memory
Sesion 3	Interpretation and discussion	Social perception (ToM)	Memory
Sesion 4	Title finding	Social perception (ToM)	Verbal and visual learning
**Third Block**	**Module 3**	**Module C**	**Module C**
Sesion 1	Repetition/paraphrasing	Thinking / problem solving	Thinking / problem solving
Sesion 2	Questions and answers	Problem-solving	Thinking / problem solving
Sesion 3	Asking questions	Problem-solving	Thinking / problem solving
Sesion 4	Focussed communication	Problem-solving	Thinking / problem solving
**Fourth Block**	**Module 4**	**Module C / Module D**	**Module C /Module D**
Sesion 1	Cognitive processing	Social schemata	Thinking / problem solving
Sesion 2	Cognitive Processing	Social schemata	Thinking / problem solving
Sesion 3	Role-playing games	Working memory	Working memory
Sesion 4	Role-playing games	Working memory	Working memory
**Fifth Block**	**Module 5**	**Module D**	**Module D**
Sesion 1	Problem identification	Attribution	Working memory
Sesion 2	Generating solutions	Attribution	Working memory
Sesion 3	Generating solutions	Attribution	Working memory
Sesion 4	Implementing solutions	Emotion regulation	Working memory

### Randomization and Switch Procedure

Following baseline assessment, patients will be randomly assigned (1:1:1 fashion) to either IPT or INT (active interventions) or Cogpack (control intervention). We expect six to eight participants in each treatment arm. Through randomization, there is the possibility that some participants will experience difficulties with their assigned treatment group. In such cases, patients will be permitted to switch to another treatment arm after 2 weeks. The sole criterion for switching intervention arm is patient preference due to excessive, respectively insufficient demands. We have chosen not to formulate explicit criteria for switching intervention arm for two reasons; first of all to empower patients in their commitment to therapy; second to prevent bias through the delayed selection of participants.

After participation in a minimum of 16 sessions (60–90 min each) in one treatment arm, the intervention will be completed; follow-up assessments will be carried out at 6 and 12 months. For a Study- Flow diagram (see Table 3 and Figure 1).

**Table 3 T3:** Schedule of enrolment, interventions, and assessments.

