### Statistical Analysis

We calculated our required sample size using G^*^Power 3.1 (51) (ANOVA: Repeated measures, three groups, four measurement points; effect size F = 0.25; < = 0.05; Power = 0.80; number of groups = 3). Based on that calculation, at least 90 participants (30 in each study arm) completing the intervention are required in order to detect small to moderate size differences. Cohen's d (effect size) will be used to compare the percentage of variation in the groups before and after treatment.

All data sets of participants will be analyzed, on an intention to treat basis. Data at baseline, second week and after the intervention, as well as at 6 and 12-months post-intervention will be considered (see Table 3). The demographic and clinical characteristics of the sample will be compared at baseline using an analysis of variance (ANOVA), except for gender and age, which will be assessed using an analysis of covariance (ANCOVA). To compare the overall effect of treatment over time in the three groups, data from the full intent to treat sample will be analyzed using a repeated-measures analysis of variance (ANOVA) with treatment as the intergroup factor and time as the intrasubject factor. *Post-hoc* analyses will be performed using Student's *t*-test for intergroup comparisons. Reported adverse effects and safety-related events will be analyzed separately as will withdrawal from the study or treatment group changes.

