The allocation of a patient to a treatment arm which does not meet his needs is considered to be unacceptable and may have detrimental effects. To avoid this situation, we have decided to allow participants to switch groups under particular conditions. We consider this approach to be both appropriate and compatible with the trial objectives since we are also interested in evaluating feasibility. In order to minimize the effect of group changes on the primary and secondary outcomes of the study, and to have similar treatment duration and number of sessions, we have chosen to conduct a second assessment prior to a (potential) change of groups. We consider 2 weeks, respectively four sessions, sufficient to determine the suitability and safety of a therapy. INT in outpatient setting shows low drop-out rates and high rates of attendance which indicates a high level of acceptance and motivation and lends support feasibility (29). Another aim of this study is to evaluate whether this also applies to inpatient settings.

Another challenge of this trial was the adaptation of a treatment (INT) designed for outpatients to an inpatient setting (29, 38). The hierarchical structure of the intervention, the density of the therapeutic sessions, and the duration of the therapy had to be taken into account together with the fact that the original therapeutic design foresees closed therapeutic groups (27). For its implementation in an inpatient setting, we subdivided the intervention into modules or blocks comprising of four sessions, allowing the participants to join the therapy at specified times thus allowing for (semi)closed groups. The disadvantage of this approach lies in the hierarchical structure of both INT and IPT interventions (23, 27), which leads participants potentially starting with a more challenging topic; to minimize this effect blocks or modules also had a bottom-up structure allowing new participants to integrate quickly into the group.

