In our study, we wish to evaluate the feasibility of a psychotherapeutic intervention in a unit specialized for the treatment of chronic and low functioning patients with a schizophrenic psychosis. Therefore, the effort required to implement such regular group psychotherapy will also be taken into account. The IPT treatment programme is manualized and has traditionally been delivered by nursing staff after an introductory seminar and workshop (23). The implementation of INT is more challenging since it also requires a trained psychotherapist (27). CGP, on the other hand, is easily implemented and requires practically no training to deliver (26, 71, 72). However, professional experience is a significant factor predicting therapy outcome. Moreover, the therapist variable is an essential factor relating to motivation to participate in the therapy and influencing drop-out rates (73–75). Consequently, all therapists running groups in this study will receive regular supervision and training.

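### IPT and INT are delivered in therapy groups, but the analysis and sample size treat patients as independent; if outcomes correlate within groups, standard errors are too small

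*Protocol article*

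**What the plan says.** **Allocation.** Under Randomization and Switch Procedure, patients are assigned individually, 1:1:1, to IPT, INT or Cogpack (CGP). The same section states: "We expect six to eight participants in each treatment arm".

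**Delivery.** The Discussion describes blocks of four sessions, "allowing the participants to join the therapy at specified times thus allowing for (semi)closed groups". Under Interventions and Therapists, IPT content "can be adapted to each group's specific needs". Each arm has its own profession: a medical resident for CGP, nurses for IPT, and therapists with a psychology and psychotherapy degree for INT. CGP is computer training whose difficulty the program adjusts for each user.

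**Acknowledged influence.** The Discussion says that "the therapist variable is an essential factor relating to motivation to participate in the therapy and influencing drop-out rates". The response is that "all therapists running groups in this study will receive regular supervision and training".

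**Analysis and size.** Statistical Analysis specifies a repeated-measures ANOVA "with treatment as the intergroup factor and time as the intrasubject factor", then Student's t-tests between arms. The sample size is 90 completers (30 per arm), from a repeated-measures ANOVA calculation with three groups, four measurements, effect size f = 0.25 and power 0.80. No therapy-group term, ICC or design effect appears anywhere in the article.

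**The concern.** Patients who attend the same sessions share peers, a leader and, for IPT, content fitted to that group. Their outcomes may therefore be more alike than those of two patients from different groups in the same arm. Individual randomisation does not remove this, because the similarity arises after allocation. An ANOVA or t-test that counts each patient as independent then attributes too little uncertainty to the arm means.

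The comparison most exposed is INT versus IPT. Both are group therapies, the Background says that no earlier trial has compared them directly, and Expected Outcomes predicts that INT will do better on cognition. With groups of about seven, 30 patients make only four or five groups per arm (30/7 = 4.3; 30/6 = 5), so one unusually good or poor group can move an arm mean noticeably.

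**Working it through.** **Inputs from the protocol article.** Completers per arm 30; f = 0.25; three arms; four measurements; power 0.80; alpha 0.05 (the symbol before 0.05 is garbled in the text).

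**Inputs inferred or assumed.** Concurrent group size g = 6 to 8: the sentence says arm, but an arm is planned at 30, so it can only sensibly mean those treated together. ICC: not given, so 0.01 to 0.10 is assumed. It is the ICC of whichever outcome quantity is tested.

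**Step 1: the stated sample size.** For the between-arm test, λ = f²·N·m / (1 + (m − 1)ρ), with m = 4 measurements, within-patient correlation ρ, and F on 2 and N − 3 degrees of freedom. The article gives neither ρ nor the type of test.
- ρ = 0.4: λ = 0.0625 × 90 × 4 / 2.2 = 10.23; power 0.81, and 90 is the required N.
- ρ = 0.5: λ = 22.5 / 2.5 = 9.0; power 0.755, and the required N is 102.

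So 90 is reproduced by the between-arm test with ρ of about 0.40 to 0.41, and can be neither confirmed nor refuted from the stated inputs. None of the variants includes clustering.

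**Step 2: INT versus IPT, both clustered.** Design effect DE = 1 + (g − 1)·ICC. True two-sided error of a nominal 5% test = 2·[1 − Φ(1.96/√DE)]. With g = 7:

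| ICC | DE | True error | Effective n per clustered arm (30/DE) |
|---|---|---|---|
| 0.01 | 1.06 | 5.7% | 28 |
| 0.02 | 1.12 | 6.4% | 27 |
| 0.05 | 1.30 | 8.6% | 23 |
| 0.10 | 1.60 | 12% | 19 |

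For g = 6 to 8 at ICC 0.05, DE is 1.25 to 1.35, the true standard error is 12 to 16% larger, and the error rate is 8.0 to 9.2%.

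**Step 3: INT or IPT versus CGP, CGP unclustered.** With equal arms, the variance of the difference is inflated by (DE + 1)/2.
- ICC 0.02: (1.12 + 1)/2 = 1.06, error 5.7%.
- ICC 0.05: (1.30 + 1)/2 = 1.15, error 6.8%.
- ICC 0.10: (1.60 + 1)/2 = 1.30, error 8.6%.

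**Step 4: simulation check.** 20,000 runs of a single outcome, three arms of 30, closed groups of 6 or of 7 and 8, all arms clustered. At ICC 0 both tests hold about 5%. At ICC 0.05 the t-test rejects in 8.0 to 8.7% and the three-arm F test in 9.0 to 10.2%. At ICC 0.10 the figures are 10.8 to 12.6% and 13.8 to 15.9%.

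**Step 5: power at 90 completers.** With ρ = 0.4, all arms clustered and ICC 0.05, λ = 10.23/1.25 = 8.18 for g = 6 (power 0.71) and 10.23/1.35 = 7.58 for g = 8 (power 0.68).

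**The case against.** **The effect needs an ICC above zero, and none is known.** This stands. A reader might infer that the standard errors are certainly too small. The article does not show that, and at ICC 0.01 the effect is slight. What it does show is a delivery that makes zero correlation doubtful and an analysis that is valid only at zero.

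**Cogpack is individual computer work.** This also stands. It would be wrong to apply an effective size of 23 to all three arms, so the contrasts with CGP are given separately and are smaller. The article does refer to therapists running groups without excepting CGP, so no clustering in that arm is itself an assumption.

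**A design effect for closed groups of 7 does not fit rolling entry.** Patients join every four sessions and stay for at least 16, so a group of 7 with even entry takes in about 7/4 = 1.75 newcomers per block. If only patients who entered together were correlated, a cohort of 2 at ICC 0.05 would give DE 1.05 and an error of about 5.6%. But patients also share sessions with those already in the group, so the running group is the more natural cluster. The figures remain approximate, and switching after four sessions blurs them further.

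**A condensed article leaves model detail to an analysis plan.** The Discussion adds that medication will be considered as a possible confounder, so treatment and time may not be the whole model. That does not supply a group term. The article names its tests and sample-size model, and both assume independence.

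**Ward conditions.** The Background's remark on disturbing behaviour might be read as evidence of correlation within therapy groups. It concerns the treatment unit, which is common to all arms, and does not support that reading.

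**Conclusion.** The concern holds conditionally. Followed as written, the analysis understates uncertainty whenever the ICC within therapy groups exceeds zero. The size runs from negligible to serious over the assumed ICC range: for INT versus IPT, from just under 6% to about 12% at a nominal 5%; for contrasts with CGP, clearly less if that arm is unclustered. The result rests on an inferred group size, an assumed ICC and a closed-group approximation. The 80% power is likewise a figure for ICC = 0; about 0.68 to 0.71 at ICC 0.05 presumes clustering in all arms and ρ of about 0.4, which the article does not state.

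A reader might also infer that a group or therapist term would separate the therapy from the person delivering it. It would not. Profession differs completely by arm, so no model term can remove that confounding; supervision and training do not remove it either.

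**What to change.** 1. Record for every participant which running therapy group (arm by block or calendar period) was attended, and its leader.
2. Replace the ANOVA and t-tests by a mixed model with a random effect for the running group first joined under randomised allocation. Make it partially nested, so that CGP carries no group variance if it is done individually. Use Kenward-Roger or similar small-sample degrees of freedom.
3. Report the ICC, and add a sensitivity analysis for overlapping membership, for example a multiple-membership model.
4. State that 80% power at 90 completers assumes ICC = 0, and give the power for a plausible range. Keeping 80% at ICC 0.05 in all arms would need about 113 to 122 completers (90 × 1.25 = 112.5; 90 × 1.35 = 121.5).
5. Word conclusions as a comparison of programmes as delivered, profession included.

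**Cost.** Randomisation and treatments are unchanged. Membership is easy to record during the trial and hard to reconstruct afterwards. The price is wider intervals, fewer degrees of freedom, and a variance component estimated imprecisely from about four or five groups per arm. If the sample size stays at 90, the lower power has to be accepted openly.
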